### Enrollment

Accrual for the LCRT study was completed in March 2012. We enrolled 403 subjects with demographic risk factors for lung cancer into a prospective multi-site, blinded LCRT study, performed bronchoscopy at enrollment, and collected NBEC and blood (buffy coat and plasma) samples from each subject (Fig. 1). Of the 403 subjects enrolled, 288 were enrolled at the time of a standard of care (SOC) bronchoscopy done for diagnostic purposes and 115 were enrolled at time of a volunteer study driven (SD) bronchoscopy. Of the 288 SOC bronchoscopies, 64 were done to evaluate for lung cancer, 34 for monitoring following lung transplantation, and the remaining 190 for a variety of indications. Of the 403 subjects enrolled, 18 were removed from the study as screen failures due to diagnosis of prevalent lung cancer at enrolling bronchoscopy or subsequent tests and one subject withdrew from the study leaving 384 subjects in the cohort. We conducted a descriptive analysis of baseline data for the 384 remaining subjects.

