### Feasibility of LCRT implementation (safety and acceptance by subjects)

The LCRT biomarker requires a one-time acquisition of NBEC through bronchial brush biopsy at the time of bronchoscopy. In addition to the LCRT study, Department of Defense Lung Cancer Research Program, and NIH recently funded other large studies assessing utility of biomarkers measured in NBEC obtained at bronchoscopy intended to more accurately determine lung cancer risk and/or to enable early lung cancer diagnosis ([name], Clinicaltrials.gov NCT01475500 CA152662 and CA102353; [name], Clinicaltrials.gov NCT02504697 DECAMP-2 and CA164783-04; [name], CA152751-05S2). Therefore, it is important to carefully evaluate the safety and comfort of this procedure, which will impact general acceptance by patients and clinicians. Based on published studies, bronchoscopy with or without biopsy is considered a safe procedure and it is used not only for medical purposes but also to conduct research [5, 41–49]. Reported complication rates (also known as serious adverse event/SAE rates) for all bronchoscopy procedures range from 0.08-1.93 % and mortality rates range from 0.004-0.045 % [50–52]. One large Japanese study of almost 50,000 patients who underwent bronchoscopy with brush biopsy in either central or peripheral airways reported a complication (SAE) rate of 0.46 %. This risk of complication is similar to the 0.28-0.32 % complication (SAE) rate reported for colonoscopy [53, 54] which is routinely used and repeated for colorectal cancer screening. Importantly, a bronchoscopy with brush biopsy limited to the *central airways* for collection of NBEC, the procedure used here, virtually eliminates risk for the primary complications reported to be associated with bronchoscopy, including pneumothorax or significant hemorrhage. Consistent with this, we observed no SAE associated with bronchoscopic brush biopsy in the subjects enrolled based on SD bronchoscopy.

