It is particularly important to assess safety and comfort in the subjects meeting accepted criteria for lung cancer screening, a group that has increased prevalence for numerous comorbidities. Results from at least one previous report have suggested that research bronchoscopy and brush biopsy can be safely performed in subjects with heavy smoking history and those with obstructive lung disease [45]. Previous guidelines have suggested that an FEV1 less than 60 % is considered a contraindication to performing research driven bronchoscopy. However, bronchoscopy in adults with stable asthma and COPD has been performed safely at lower values of FEV1 [55]. Pulmonary function test data were available for more than 75 % of the subjects enrolled here (290 of 384 subjects). One hundred fifty-seven had clinical COPD and more than 70 % had GOLD stage 2 or worse (Table 2). Additionally, 9 % of enrolled subjects had a history of interstitial lung disease, 9 % were single-lung transplant recipients and a small percentage had other pulmonary disease (Additional file 3: Table S3) and bronchoscopy was safely performed on all of them. Specifically, no complications (SAEs) were associated with bronchoscopic brushing and sample collection in either standard of care (SOC) or study driven (SD) group.

In summary, bronchoscopic brush of the central airways to collect NBEC for lung cancer risk analysis was safe and well-tolerated in this study of subjects demographically at risk for lung cancer, including those with significant co-morbid conditions. Because the AE rate was much lower than that reported for routinely used screening colonoscopy [53] we expect that this procedure will be acceptable to patients and clinicians if the LCRT or other tests in development are validated to identify subjects with increased risk for lung cancer and/or early stage lung cancer.

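### Zero brushing-associated SAEs in about 400 subjects does not show a rate much lower than colonoscopy's 0.28–0.32 %, and the sentence compares an AE rate with an SAE rate

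*Protocol article*

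**What the plan says.** All the relevant statements are in the Discussion section on feasibility of LCRT implementation.

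- **Published rates.** A large series of bronchoscopy with brush biopsy, almost 50,000 patients, "reported a complication (SAE) rate of 0.46" per cent. The article then comments: "This risk of complication is similar to the 0.28-0.32 % complication (SAE) rate reported for colonoscopy".
- **Own data.** For volunteers, "we observed no SAE associated with bronchoscopic brush biopsy in the subjects enrolled based on SD bronchoscopy". For everyone, "no complications (SAEs) were associated with bronchoscopic brushing and sample collection in either standard of care (SOC) or study driven (SD) group".
- **Conclusion.** "Because the AE rate was much lower than that reported for routinely used screening colonoscopy", the authors expect the procedure to be acceptable to patients and clinicians. No count, denominator or interval accompanies this sentence. It cites one of the two sources given for the colonoscopy range.

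The denominators are in the Results, under Enrollment: "Of the 403 subjects enrolled, 288 were enrolled at the time of a standard of care (SOC) bronchoscopy done for diagnostic purposes" and the other 115 at a study-driven (SD) bronchoscopy. After 18 screen failures, "one subject withdrew from the study leaving 384 subjects in the cohort".

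**The concern.** Safety at day 30 is a secondary endpoint (Methods, Study design), and reporting it is a stated purpose of the article. The sentence at issue is the reason given for expecting patients and clinicians to accept a bronchoscopy for risk testing. It turns an observed count of zero into a claim about the size of the underlying rate relative to a rare-event comparator. At a rate near 0.3 %, a sample of about 400 is expected to yield only about one event, so seeing none says little about whether the true rate is lower.

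The terms also do not match. The Methods section on safety analysis treats AEs (including fatigue, sore throat and hoarseness) and SAEs as different categories, yet an AE rate is set against what the article itself labels a complication (SAE) rate.

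**Working it through.** The article gives no calculation behind the comparison, so there is no figure to reproduce. The check takes the SAE reading, the only one with a colonoscopy figure in the text.

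**Inputs**
- Events: 0 brushing-associated SAEs, standard-of-care (SOC) and SD groups together (Discussion).
- Comparator: "0.28-0.32 % complication (SAE) rate reported for colonoscopy", so p = 0.0028 to 0.0032.
- Denominators: 403 had the procedure (288 SOC + 115 SD); 403 − 18 − 1 = 384 remained (269 SOC + 115 SD). The Discussion does not say which one the zero refers to, so both are used. Under the Methods, a subject counted as enrolled on undergoing the brushing, which makes 403 the natural safety denominator.

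**Step 1: exact upper limit for zero events.** Two-sided 95 %: 1 − 0.025^(1/n). One-sided 95 %: 1 − 0.05^(1/n).

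| n | two-sided | one-sided |
|---|---|---|
| 403 | 0.91 % | 0.74 % |
| 384 | 0.96 % | 0.78 % |
| 115 (SD only) | 3.16 % | 2.57 % |

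Every limit lies above 0.32 %. For n = 403 the two-sided limit is 0.91/0.32 = 2.8 to 0.91/0.28 = 3.3 times the colonoscopy rate.

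**Step 2: chance of zero events if the true rate equals colonoscopy's.** Expected events = n × p; P(0) = (1 − p)^n.

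| n | expected at 0.28 % / 0.32 % | P(0) at 0.28 % / 0.32 % |
|---|---|---|
| 403 | 1.13 / 1.29 | 32.3 % / 27.5 % |
| 384 | 1.08 / 1.23 | 34.1 % / 29.2 % |
| 115 | 0.32 / 0.37 | 72.4 % / 69.2 % |

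**Step 3: event-free subjects needed to bring the upper limit down to the comparator.** n = ln(0.025)/ln(1 − p) gives 1,151 at 0.32 % and 1,316 at 0.28 % (two-sided). The one-sided version, with ln(0.05), gives 935 and 1,069. Either way, 403 is less than half of what is needed.

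**Step 4: consistency with the article's own yardstick.** The Discussion calls 0.46 % similar to 0.28–0.32 %. At a true rate of 0.46 %, zero events would occur with probability 15.6 % (n = 403) or 17.0 % (n = 384). The data therefore do not exclude even the brush-biopsy rate that the article treats as equivalent to colonoscopy's.

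**The case against.** **An observed 0 % is below 0.28 %.** As a description of the sample this is correct. But the sentence uses it to predict acceptance in future use, which depends on the underlying rate, and the word *much* has no support.

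**The case for safety does not rest on this sentence alone.** The Discussion also cites the series of almost 50,000 patients and argues that restricting brushing to the central airways removes the main risks. The Abstract and Conclusions say only that collection was safe and well tolerated and do not repeat the colonoscopy comparison. This stands and limits the reach of the point. The central-airway argument is a mechanism, though, not something these data showed.

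**AE may really mean AE.** Then the numerator could lie in text not available here and the comparator in the cited source. A part of the Results between the lung transplant and repository sections, probably the safety results, could not be checked. So the absence of an interval is established for the Discussion only, and the arithmetic applies only to the SAE reading.

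**Stronger readings to avoid.** A reader might take the 115 SD subjects as the relevant group and lead with a limit of 3.2 %, about ten times colonoscopy's rate. The article does not support this: its section comparing SOC and SD bronchoscopy places both groups in the intended population, so the SD figure describes one of two groups. A reader might also infer that the procedure is as risky as colonoscopy, or riskier. Zero events do not show that either; they leave the question open.

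**Conclusion.** The point holds on the SAE reading. Zero attributed SAEs in 384–403 subjects is compatible with a true rate of up to 0.91–0.96 % (exact two-sided 95 %), and it would arise 27–34 % of the time at colonoscopy's own rate. A rate much lower than colonoscopy's is therefore not established. The result does not depend on which denominator is used, on one- or two-sided limits, or on which end of the 0.28–0.32 % range is taken. The mismatch between AE and SAE is a separate fault of wording and stands on the text alone.

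The conclusion assumes that the zero count in the Discussion is complete and that the published range is the comparator intended. It concerns one safety statement. The primary endpoint, sample size and follow-up are untouched.

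**What to change.** In the closing paragraph of the feasibility section:

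1. Delete the claim of a much lower rate.
2. State that no brushing-associated SAE was observed (0/403, exact two-sided 95 % upper limit 0.9 %) and that this does not exclude a rate like that reported for colonoscopy. If the safety denominator was 384, the limit is 0.96 %.
3. Compare SAE with SAE and use that term throughout. If an AE comparison was intended, give the AE count and a colonoscopy AE rate on the same definition.
4. Add 0/115 for SD bronchoscopy (upper limit 3.2 %) as a secondary subgroup figure, since these subjects are one of the two intended groups.
5. If the safety results already give counts and limits, refer to them rather than repeat them.

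The cost is one rewritten sentence and two confidence limits. No new data or analysis is needed, but the safety statement becomes less favourable.

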### COPD characteristics of LCRT Cohort

The enrolled cohort had a high fraction of COPD based on PFT criteria. This is important because COPD is an independent risk factor for lung cancer [30–38]. Notably, using PFT data (FEV1/FVC <0.7) as the diagnostic criterion, one-third of individuals in this study misclassified their COPD status on the enrollment survey self-report. This is consistent with multiple reports of data acquisition through self-report leading to either misclassification or under-diagnosis of COPD [56–60]. Some of this misclassification could be due to patient being told they have COPD on the basis of radiographic imaging while the PFT data do not meet criteria for COPD diagnosis. Additionally, a portion of the subjects here underwent PFT at the time of enrollment that revealed COPD for the first time because the subject had not been tested prior to enrollment in the study. Given the importance of accurate COPD diagnosis, we plan to obtain both chest CT and PFT data from each subject at each subsequent follow-up. We will then evaluate COPD based on CT (presence of emphysema and/or bronchial thickening) or PFT criteria alone, or in combination as a risk factor for lung cancer.

### LCRT cohort and biospecimen repository as a resource for subsequent studies

As presented here, the LCRT cohort is well characterized with respect to demographic characteristics. In addition, NBEC and matching blood samples were collected from each subject. Each subject had a baseline CT scan and pulmonary function test (PFT) data are available for 76 % of individuals. It is planned to obtain a repeat PFT and CT scan on all subjects at each subsequent follow-up. This information will enable longitudinal assessment for rate of decline in pulmonary function by both physiologic and radiographic measures and to assess for presence or absence of lung cancer. More than 90 % of samples assessed so far passed QC quality and quantity criteria for reliable LCRT measurement. The NBEC and matching blood samples collected in this study are archived and the majority of subjects have given consent for use of samples remaining after LCRT analysis for future IRB approved studies. Currently, we are using NBEC gene expression data and genotyping data from matched peripheral blood cell gDNA to identify proximate phenotypic biomarkers for COPD risk and additional biomarkers for hereditary lung cancer risk. We are integrating these data with COPD genome wide association study (GWAS) data from the Lung Health Study and the COPDgene study available online at NCI dbGAP.

## Conclusions

The demographic composition of the enrolled group is representative of the population for which the LCRT is intended. Specifically, based on baseline population characteristics we expect lung cancer incidence in this cohort to be representative of the population eligible for LDCT lung cancer screening. Collection of NBEC by bronchial brush biopsy/bronchoscopy was safe and well-tolerated in this population. These findings support the feasibility of testing LCRT clinical utility in this prospective study. If validated, the LCRT has the potential to significantly narrow the population of individuals requiring annual low-dose helical CT screening for early detection of lung cancer and to enable safe delay the onset of screening for individuals with results indicating low lung cancer risk. For these individuals, the small risk incurred by undergoing once in a lifetime bronchoscopic sample collection for LCRT may be offset by a reduction in their CT-related risks. The LCRT biospecimen repository will enable additional studies of genetic basis for COPD and/or lung cancer risk.

## Abbreviations

AE: Adverse event
COPD: Chronic obstructive pulmonary disease
FEV1: Forced expiratory volume in 1 second
FVC: Forced vital capacity
GWAS: Genome wide association study
LCRT: Lung Cancer Risk Test
LDCT: Low dose computed tomography
NBEC: Normal bronchial epithelial cells
PFT: Pulmonary function test
SAE: Serious adverse event
SNP: Single nucleotide polymorphism
SD: Study driven
SOC: Standard of care
USPSTF: United States Preventive Services Task Force
